## Abstract

**Objective::**

Curcumin is a safe phytochemical with antioxidant, anti-inflammatory, antidiabetic, and lipid-lowering effects. This study aims to investigate the efficacy of curcumin-piperine in non-proliferative diabetic retinopathy.

**Materials and Methods::**

In this double-blind randomized trial, 60 diabetic retinopathy patients after meeting the inclusion criteria will be randomly assigned to two groups of curcumin-piperine supplementation (1000 mg per day for 12 weeks) or receiving placebo. The density of small blood vessels in the retina by optical coherence tomography angiography (OCTA), fasting blood glucose, triglyceride, renal indices (blood urea nitrogen and creatinine), high-sensitivity C-reactive protein, total antioxidant capacity, total oxidant status, body mass index, waist circumference, and weight will be measured.

**Conclusion::**

If the beneficial effects of curcumin on diabetic retinopathy are observed, this safe, this natural and inexpensive herbal supplement can be considered a therapeutic solution in these patients.

## Introduction

Diabetes can cause various microvascular complications, especially diabetic retinopathy (DR) (Behl et al., 2016). The number of people with diabetes is expected to increase from about 382 million in 2013 to 592 million in 2035, so, the risk of developing diabetic retinopathy will increase in the coming decades (Guariguata et al., 2014; Nanditha et al., 2016). DR greatly affects the quality of life and interferes with daily activities (Simó-Servat et al., 2019). Most cases of blindness and visual impairment in working-age adults are due to DR (Yoon et al., 2006). DR has two distinct levels, including the early stage of non-proliferative diabetic retinopathy (NPDR) and the advanced stage of proliferative diabetic retinopathy (PDR) (Mohamed et al., 2007). NPDR is characterized by microaneurysms, retinal hemorrhages, and microvascular abnormalities, and PDR is associated with the pathological pre-retinal formation of new vessels (neovascularization and angiogenesis) (Stitt et al., 2016). The resulting vessels have thin and fragile walls, and the risk of bleeding from these vessels is high; these conditions can lead to sudden and complete blindness (Brownlee, 2001). 

Hyperglycemia is one of the major risk factors for DR. Exposure of retinal capillary endothelial cells to high glucose levels stimulates the formation of free radicals (oxidative stress) (Behl et al., 2016). Controlling blood sugar and systemic blood pressure reduces the risk of microvascular complications of diabetes (Behl et al., 2016). Inflammation and oxidative stress also play an important role in diabetic patients (Lontchi-Yimagou et al., 2013; Karam et al., 2017). 

Current therapies for DR include the use of intravitreal drug agents, laser photocoagulation, and vitreous surgery, all of which focus on the management of microvascular complications (Gonzalez et al., 2016). Vascular endothelial growth factor (VEGF) causes angiogenesis by affecting the vessel wall, thus, playing a vital role in the pathogenesis of DR (Behl et al., 2016). At present, intravitreal anti-VEGF drugs are the primary treatment in various stages of DR (Yoon et al., 2006). Although they improve vision in many retinal diseases, side effects are common (Nguyen et al., 2012; Ip et al., 2008). One of the side effects of anti-VEGF injection is intraocular inflammation (Tolentino, 2011). Moreover, its high cost has placed a significant burden on the healthcare system (Choi et al., 2013). Another method is laser therapy which may be associated with retinal damage (David et al., 2012). Given these concerns, finding practical, effective, inexpensive, and affordable treatments with minimal side effects is essential.

Plants containing polyphenols have traditionally been used as antidiabetic agents (Watal et al., 2014; Srinivasan, 2005). Among these, plants that have the most negligible side effects are receiving more attention (Nabavi et al., 2015). Curcumin, the biologically active substance in turmeric, is a low molecular weight hydrophobic flavonoid with numerous health benefits including antioxidant and anti-inflammatory activities (Jeenger et al., 2015; Neerati et al., 2014; Mohajeri et al., 2020; Parsamanesh et al., 2018; Farhood et al., 2019; Gorabi et al., 2019; Mortezaee et al., 2019; Shakeri et al., 2019). No significant adverse effects are associated with supplementation with curcumin, even at doses above 8 g/day (Mirzaei et al., 2017). Many regulatory proteins, including chemokines, interleukins, hematopoietic growth factors, and transcription factors, are modulated by curcumin, thus reducing the inflammatory process (Peddada et al., 2019). In several studies, curcumin has been shown to downregulate tumor necrosis factor (TNF) -α (Li et al., 2013) and C-reactive protein (Adibian et al., 2019).

Curcumin supplementation improved glycemic factors, low-density lipoprotein, very low-density lipoprotein, and triglycerides in patients with diabetes (Neerati et al., 2014). It also significantly lowered blood glucose levels (Nabavi et al., 2015) and modulated retinal disorders in diabetic rats by preventing retinal thinning, apoptosis of retinal ganglion cells and inner nuclear layer cells, and thickening the retinal capillary basement membrane (Yang et al., 2018). In obese mice, curcumin consumption significantly improved glycemic status (blood glucose, glucose tolerance, and, HbA1C) and insulin sensitivity (Weisberg et al., 2008). 

The effectiveness of curcumin on diabetes has been discussed in several recent meta-analyses. In a way that curcumin improves blood sugar, and lipid factors, and reduce insulin resistance, it has a beneficial effect on improving and preventing the progression of diabetes (Altobelli et al., 2021; Zhang et al., 2021; Poolsup et al., 2019). In a trial study, the efficacy of Meriva (each tablet containing 500 mg of Meriva equivalent to 100 mg of curcumin) was evaluated in patients with DR. The results of this study showed an improvement in arterial vascular response and peripheral edema score (Steigerwalt et al., 2012).

Curcumin has low bioavailability due to its low solubility in aqueous solvents and instability at physiological pH which limit its use in clinics (Anand et al., 2007). Interestingly, the combination of curcumin with piperine (an alkaloid derived from the plant *Piper nigrum* L.) has better gastrointestinal absorption and reduces curcumin's systemic excretion. Piperine increases the bioavailability of curcumin by binding to the enzyme glucuronidase in the intestine, preventing glucuronidation and reducing the excretion of curcumin from the stool (Kaur, 2012).

Optical Coherence Tomography Angiography (OCTA) is a new noninvasive, colorless eye volume imaging technique (Matsunaga et al., 2014) used to evaluate common eye diseases such as acute macular degeneration, DR, arterial and venous occlusion, and glaucoma (Carlo et al., 2015). Optical coherence tomography (OCT) has been used since 1991 as a suitable fraternal imaging tool to analyze eye disorders. However, it is not able to provide sufficient and appropriate information about retinal and choroidal vasculature (Fingler et al., 2007), while OCTA can display structural and functional data (including blood flow) simultaneously (Schwartz et al., 2014). Compared to other eye imaging modalities, including FA (Fluorescein angiography) and ICGA (indocyanine green angiography), OCTA has many benefits. For example, it is noninvasive, achieves good volume scans in a matter of seconds, uses motion contrast instead of intravenous dye, and provides more accurate information (Matsunaga et al., 2014).

To our knowledge, no study assessed the effect of curcumin supplementation on macular vascular density in OCTA in patients with DR. Thus, this study aims to investigate the efficacy of curcumin-piperine co-supplementation on cardiometabolic, inflammatory, and oxidative stress factors and macular vascular density in OCTA in patients with non-proliferative diabetic retinopathy. 

## Materials and Methods

**Trial design**

This is a randomized, placebo-controlled, double-blind, parallel-arm clinical trial performed in university hospitals affiliated of Isfahan University of Medical Sciences, Isfahan, Iran. Recruitment has started in February 2022.

Sixty patients in the age group of 30 and 65 years old, diagnosed with DR with the approval of an ophthalmologist, imaging, or CT scan will be enrolled (According to Figure 1). Patients will be randomly assigned in a 1:1 ratio into two groups: 1) Placebo capsules, each containing 505 mg of maltodextrin, two capsules/day, 2) Curcumin-piperine capsules, each containing 500 mg of curcumin and 5 mg of piperine, two capsules/day. Patients will be asked to consume capsules after breakfast and dinner for 12 weeks.

**Figure F1:**
[figure not shown]
Participant flow diagram according to the Consolidated Standards of Reporting Trials (CONSORT) 2010 statement

**Participants **

**Inclusion criteria**

Inclusion criteria are 30 to 65 years of age, diagnosis of DR with the approval of an ophthalmologist, imaging, CT scan or PCR, and definitive diagnosis of diabetes by a diabetic physician (fasting blood glucose above 126 mg/dl, measured twice, or HbA1C greater than or equal to 6.5%).

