**Exclusion criteria**

Exclusion criteria are allergies to herbal products such as turmeric and pepper, following a special diet in the last 3 months, taking anticoagulants such as heparin, warfarin, or aspirin, insulin consumption, pregnancy or lactation, taking medications or herbal supplements in the last 3 months, current use of anti-VEGF, use of treatments including laser therapy, eye surgery, and intraocular injections, glaucoma, macular edema, and ocular uveitis, or having certain diseases such as congenital diseases, type 1 diabetes, immunodeficiency, cancer, or uncontrolled diabetes. Patient will also be excluded if they are dissatisfied to continue the intervention, taking less than 80% of curcumin piperine supplement, reporting any adverse events after taking the supplement, or if other treatments of the patient, including treatment of hypertension, hyperlipidemia, etc. change during the treatment period. 

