**Sample size**

The most important finding of this study is the effects of curcumin on the accumulation of small blood vessels in the eye area (based on OCTA findings). Due to the novelty of this evaluation method, according to the researcher's knowledge, there is no similar study in this regard. Therefore, the sample size is calculated based on fasting blood glucose in a previous study (Seyyedebrahimi et al., 2018) as follows: 

Based on 80% power, an α level of 0.05, and a potential dropout rate of 10%, 60 participants (i.e. 30 participants in each group) would be required. The formula n=2[(Z1-α/2+Z1-β)2×S2]/ Δ2=2[(1.96+0.84)^2^× (27)^2^]/ (25)^2^ was used to calculate the sample size.

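### The objective is non-proliferative retinopathy, but the written criteria require only diabetic retinopathy of unstated stage and do not exclude untreated proliferative disease

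*Protocol article*

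**What the plan says.** The question is restricted by stage. The Abstract's objective reads "This study aims to investigate the efficacy of curcumin-piperine in non-proliferative diabetic retinopathy", and the Introduction closes with an aim that covers "macular vascular density in OCTA in patients with non-proliferative diabetic retinopathy".

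The Introduction also fixes what the unqualified term means: "DR has two distinct levels, including the early stage of non-proliferative diabetic retinopathy (NPDR) and the advanced stage of proliferative diabetic retinopathy (PDR".

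Enrolment is described in three places, each time with the unqualified term:

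- Abstract, Materials and Methods: "60 diabetic retinopathy patients after meeting the inclusion criteria".
- Trial design: "diagnosed with DR with the approval of an ophthalmologist, imaging, or CT scan will be enrolled".
- Inclusion criteria: "diagnosis of DR with the approval of an ophthalmologist, imaging, CT scan or PCR".

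None of these gives a stage, a grade or a severity scale. The eye-related exclusions are "current use of anti-VEGF, use of treatments including laser therapy, eye surgery, and intraocular injections, glaucoma, macular edema, and ocular uveitis". Proliferative retinopathy is not in that list.

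**The concern.** Eligibility determines whom the result describes. Here the objective names one of the two stages that the article distinguishes, and the criteria name both together. A result from a mixed sample could not be reported cleanly as a finding in NPDR.

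The Sample size section calls the OCTA vessel finding the most important one of the study. The Introduction separates the stages by their vascular features: microvascular abnormalities in NPDR, and new vessels forming in front of the retina in PDR. It is therefore reasonable to expect that stage could add spread to a vessel-density outcome. Randomization is blocked on age and gender, not on stage, so in a trial of 60 the balance of stage between arms is left to chance. If stage is not recorded, the analysis cannot account for it.

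The list of diagnostic routes raises a second, smaller question: what evidence establishes the retinopathy at entry?

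**Working it through.** No figure in the plan bears on this point, so the check is a reading of the criteria against the aim.

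**Step 1. Does a patient with PDR meet the inclusion criteria?** They have three parts: age 30 to 65, a diagnosis of DR, and a confirmed diagnosis of diabetes (by fasting glucose or HbA1C). By the Introduction's definition, PDR is DR. Such a patient can satisfy all three.

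**Step 2. Do the exclusions remove that patient?** The Introduction lists the current therapies for DR as intravitreal agents, laser and vitreous surgery. Each matches an exclusion:

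| Situation | Removed by the written exclusions? |
|---|---|
| On anti-VEGF, or given intraocular injections | Yes |
| Treated by laser or eye surgery | Yes |
| With macular edema, glaucoma or uveitis | Yes |
| Insulin use, type 1 or uncontrolled diabetes | Yes |
| Untreated PDR with none of the above | No |

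The exclusions act on treatment, on other eye disease and on general health. None acts on the stage of retinopathy. The last row stays eligible, provided that no other general exclusion applies.

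**Step 3. Are the diagnostic routes consistent?** Trial design lists an ophthalmologist, imaging or CT. Inclusion criteria lists the same routes and adds PCR. The article does not say how CT or PCR would establish retinopathy or its stage. CT may be a slip for OCT, but it stands in both places, and PCR has no such explanation.

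**Step 4. Can the consequence be sized?** Let p be the share of PDR, and let Δ_N and Δ_P be the treatment effects on vessel density in NPDR and PDR. With p equal in both arms, the pooled effect is (1 − p)Δ_N + pΔ_P. This equals Δ_N only if p = 0 or the two effects are the same. If σ² is the variance of the outcome within a stage, and d is the difference in mean outcome between stages, the variance within an arm is σ² + p(1 − p)d². Mixing therefore adds variance whenever d is not zero.

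The article gives none of p, Δ_N, Δ_P, σ or d. Its only standard deviation and difference, 27 and 25, are for fasting glucose. The direction of the variance term follows from the formula, but its size is unknown.

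**The case against.** The strongest reply is that the gap is narrow. Patients who have had any of the usual retinopathy treatments are out, as are those with macular edema, insulin use or uncontrolled diabetes. What remains is untreated PDR in an otherwise eligible patient, and nothing shows that such patients are common. This stands as a limit on the size of the problem. It does not remove the contradiction, because a stated rule still admits a group that the stated aim leaves out.

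One may also say that the article uses DR as shorthand for NPDR. But the Introduction defines the term to include both stages, and the eligibility sections are otherwise detailed, with glucose thresholds, washout periods and individual eye diseases. The Abstract's conclusion and the Discussion also speak of diabetic retinopathy in general, so the text does not settle which population is meant.

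On the diagnostic list, a reader might infer that CT or PCR alone suffices for entry. The text does not establish that. The ophthalmologist's approval can be read as governing the whole list, and the OCTA evaluation section has an ophthalmologist image patients before the study. Under either reading, the stage is unspecified and the two lists differ.

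Finally, randomization still gives a fair comparison for whoever is enrolled. That is correct. The loss is in fit to the stated population and possibly in precision; it is not bias between arms.

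**Conclusion.** The concern holds as a contradiction between the objective and the eligibility rules: the population that may be enrolled is wider than the one about which the trial means to conclude. The likely consequences are a weaker NPDR-specific conclusion and possibly more variability in the OCTA outcome, by an amount that the article does not allow one to compute. This conclusion rests on the article's text. Its figures, including the flow diagrams, were not available.

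Two stronger readings are not supported:

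- A reader might infer that PDR and NPDR would respond in opposite directions, so that pooling cancels or reverses the effect. The article describes new vessels in PDR as pre-retinal, whereas the outcome is the density of small vessels in the retina. It does not say that the former enter the latter. The VEGF mechanism comes from mouse data and an explanatory figure. Even if the responses were assumed equal and opposite, the pooled effect would be (1 − p) − p = 1 − 2p of the NPDR effect, and the sign would change only if PDR exceeded 50% of the sample.
- A reader might infer that patients with advanced disease are denied care during the 12-week placebo comparison. No section withholds standard treatment. The exclusion criteria say that patients whose other treatments change are excluded.

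**What to change.** Reconcile the Abstract, Introduction, Trial design, Inclusion criteria and Exclusion criteria:

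1. In Trial design and Inclusion criteria, state non-proliferative DR confirmed by an ophthalmologist on retinal examination or imaging, and use the same diagnostic list in both.
2. Correct or remove CT scan and PCR.
3. Add proliferative DR to the exclusions.
4. If all DR is in fact intended, leave the criteria unstaged, still make the diagnostic lists agree, and change the objective and aim.

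Recruitment began in February 2022, so rewording alone does not deal with patients already enrolled. For them, record the stage from the baseline examination, by someone blinded to allocation. Before unblinding, specify the NPDR analysis. It should stand alongside the planned intention-to-treat analysis of all randomized patients and not replace it.

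The cost is a slightly narrower recruitment pool and possibly an NPDR analysis set somewhat smaller than 60. The added work should be small, since an ophthalmologist already images patients at baseline. This assumes that the baseline records of those already enrolled are sufficient to assign a stage.

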**Exclusion criteria**

Exclusion criteria are allergies to herbal products such as turmeric and pepper, following a special diet in the last 3 months, taking anticoagulants such as heparin, warfarin, or aspirin, insulin consumption, pregnancy or lactation, taking medications or herbal supplements in the last 3 months, current use of anti-VEGF, use of treatments including laser therapy, eye surgery, and intraocular injections, glaucoma, macular edema, and ocular uveitis, or having certain diseases such as congenital diseases, type 1 diabetes, immunodeficiency, cancer, or uncontrolled diabetes. Patient will also be excluded if they are dissatisfied to continue the intervention, taking less than 80% of curcumin piperine supplement, reporting any adverse events after taking the supplement, or if other treatments of the patient, including treatment of hypertension, hyperlipidemia, etc. change during the treatment period. 

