**Randomization and interventions**

Participants will be randomized using four blocks based on age and gender in 1:1 ratio into two groups using computer generated randomization (https://www.sealedenvelope.com/simple-randomiser/v1/lists) (According to Figure 2(. Allocation concealment will be performed by sequentially numbered containers.

Group 1 consists of 30 patients who will be received two curcumin-piperine capsules per day for 12 weeks (each capsule contains 500 mg curcumin and 5 mg piperine; a total of 1000 mg curcumin and 10 mg piperine per day). 

Group 2 will be the control and consists of 30 patients who will be received two placebo capsules per day (maltodextrin) (each capsule contains 505 mg maltodextrin; a total of 1010 mg of maltodextrin per day) for 12 weeks. 

Study compliance will be evaluated by giving a supplement box to the participants every month. At the end of every month, the number of unused supplements will be counted and recorded. Patients will be reminded to take supplements weekly by phone and SMS during the study. Participants will be excluded from the study if they take less than 80% of the supplements during the study.

If a patient misses a dose of the supplement, it is recommended that they take the supplement immediately after the reminder. If much time has elapsed since the allotted time for consumption one dose will be considered missing. 

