**Measurements and outcomes**

Demographic variables (including age, sex, marital status, smoking, medical history and history, level of education, occupation, supplementation, and medication) will be collected from all participants by completing a general information questionnaire at the beginning of the trial. Anthropometric indices (waist circumference, weight, and BMI) will be measured at the beginning and at the end of the study. Bodyweight will be measured using a digital scale (Seca scale, Germany) at approximately 0.1 kg in the morning on an empty stomach without shoes and with minimal clothing. Waist circumference and height will be measured by an inelastic meter with an accuracy of 0.1 cm.

Fasting blood samples (10 ml) will be collected at baseline and 12 weeks after intervention at 8:00 am to check blood factors. high-sensitivity C-reactive protein (hs-CRP), blood glucose, triglyceride, and renal indices (blood urea nitrogen and creatinine) using the ELISA kit, also, oxidative stress indices including total antioxidant capacity (TAC) and total oxidant status (TOS) using the colorimetric method by commercial Kiazist kits (Tehran, Iran) will be measured at the beginning of the study and repeated 12 weeks after the intervention in groups A and B (Table 1).

**Table 1 T1:** Time line and applied tests. BMI: Body mass index, WC: Waist circumference, OCTA: Optical coherence tomography angiography, hs-CRP: high-sensitivity C-reactive protein, TG: Triglyceride, BUN: Blood urea nitrogen, TAC: Total antioxidant capacity, TOS: total oxidant status

[figure not shown]

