**Safety**

In previous studies, no significant risk was observed during supplementation with curcumin, even at doses above 8 g/day (Mirzaei et al., 2017). However, if any adverse side effects are reported after taking, the supplements will be stopped immediately.

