**Statistical methods**

The present study will report quantitative variables as average (standard deviation) and qualitative variables as number (percentage). The normality of the distribution of quantitative variables will be assessed using the skewness index and the Q-Q plot diagram. Intragroup analyses will be performed using paired t-test and intergroup analyses using independent t-test and ANCOVA. The distribution of qualitative variables will be compared between the two groups using the chi-square test. SPSS software version 22 will be used to analyze the data with a significance level of p<0.05. The analysis will eventually be performed in the form of Intention-To-Treat (ITT) and Per-Protocol (PP).

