**Figure 3 F3:**
[figure not shown]
Possible effects of curcumin on the improvement of diabetic retinopathy. (curcumin-piperine can improve diabetic retinopathy by improving inflammatory factors, reducing free radicals, anti-VEGF effects, increasing insulin sensitivity, and improving lipid factors)

The most important strength of our protocol is that if significant benefits emerge, as this treatment requires very low costs and displays minimal side effects, it can be easily used clinically, and adherence will be high. The main limitation of our protocol is that the intervention time is relatively short. In addition, due to ethical issues, we will not be able to study the effect of curcumin-piperine alone. Also, due to economic constraints, it is impossible to measure important factors such as TNF-α, IL-6, and HbA1C. Another limitation is that due to lack of funding, it is not possible for us to consider a blood biomarker of the curcumin to assess adherence to supplements.

Due to the lack of medical care and pharmacological agents for DR, if this trial shows beneficial effects of curcumin on patients with diabetic retinopathy, this dietary supplement would be considered as a safe, natural and inexpensive supplement with minimal side effects for this condition. In addition to this study, in future, more well-designed clinical trials will be needed to clarify the effects of curcumin on DR and to determine the optimum dose and type of curcumin for the intervention.

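### Four events that occur after randomisation are written as reasons to exclude patients, which conflicts with the promised intention-to-treat analysis and can bias the comparison

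*Protocol article*

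**What the plan says.** **Exclusion criteria.** After the baseline criteria the section continues: "Patient will also be excluded if they are dissatisfied to continue the intervention". It then adds "taking less than 80% of curcumin piperine supplement, reporting any adverse events after taking the supplement, or if other treatments of the patient", giving hypertension and hyperlipidaemia treatment as examples, "change during the treatment period".

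**Randomization and interventions.** The adherence rule is repeated with its consequence: "Participants will be excluded from the study if they take less than 80% of the supplements during the study". Adherence is assessed from monthly counts of unused supplements.

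**Safety.** The wording here is different: "if any adverse side effects are reported after taking, the supplements will be stopped immediately". Nothing in that section says the patient leaves the study.

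**Measurements and outcomes; OCTA evaluation.** "Fasting blood samples (10 ml) will be collected at baseline and 12 weeks after intervention". Anthropometry is taken at the beginning and end, and OCTA before and after the study. The text describes no intermediate outcome assessment.

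**Statistical methods.** "The analysis will eventually be performed in the form of Intention-To-Treat (ITT) and Per-Protocol (PP". Neither set is described and neither is named as primary.

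**Discussion.** If benefit is shown, "this dietary supplement would be considered as a safe, natural and inexpensive supplement with minimal side effects for this condition".

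**The concern.** ITT means that every randomised patient counts in the assigned group, whatever happens afterwards. The four events can arise only once capsules are being taken. A rule that removes patients for them belongs to the definition of a per-protocol set, but here it is written as removal from the trial.

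The reasons are unlikely to be neutral. Adverse events and dissatisfaction can be caused by the capsules. A change in other treatment can follow deterioration. If such patients go in different numbers, or for different reasons, in the two arms, those who remain are no longer the groups that randomisation made comparable. An analysis cannot repair this later if the week-12 measurements were never taken.

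Follow-up for safety also stops for the patients in whom it matters most.

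**Working it through.** **1. The passages side by side**

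| Event | Exclusion criteria | Elsewhere in the protocol |
|---|---|---|
| Dissatisfaction | excluded | not addressed |
| Intake below 80% | excluded; wording names only the active supplement | excluded from the study; wording covers the supplements generally (Randomization and interventions) |
| Any adverse event | excluded | supplements stopped (Safety) |
| Change of other treatment | excluded | not addressed |
| Analysis | – | ITT and PP (Statistical methods) |

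Three different things are run together: stopping capsules, leaving the study, and leaving the PP set. No sentence says that an excluded patient still has the week-12 assessment or stays in the ITT set.

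**2. The plan's own sample-size figure**

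Inputs from Sample size: SD 27, difference 25, z-values 1.96 and 0.84, dropout 10%.

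n = 2 × (1.96 + 0.84)² × 27² / 25² = 18.29, so 19 per arm. Allowing for dropout, 19/0.9 = 21.1, so 22 per arm. The stated 30 per arm does not follow from these inputs. That is a separate matter, but it means there is slack.

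**3. Does exclusion threaten power?**

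The planned effect is 25/27 = 0.926 SD. Two-sided 5% test, assumed exclusion rates:

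| Excluded per arm | n per arm | Power (normal approximation) |
|---|---|---|
| 0% | 30 | 94.8% |
| 10% | 27 | 92.5% |
| 20% | 24 | 89.4% |
| 30% | 21 | 85.1% |
| 40% | 18 | 79.3% |

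An exact t-test calculation at 21 per arm gives 83.3%. Up to about 30% exclusion, power stays above 80%.

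**4. How large could the bias be?**

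The protocol gives no exclusion rates, so this step is illustrative. Assumptions: no true effect, SD 27 mg/dl, 30 per arm, and exclusion more likely with a poor outcome, with correlation ρ between the tendency to be excluded and the outcome. Results are from 20,000 simulated trials per scenario, analysed by independent t-test.

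| Excluded, active vs placebo | ρ | Spurious difference (mg/dl) | Type I error |
|---|---|---|---|
| 10% vs 10% | 0.3 / 0.5 | about 0 / about 0 | 5.2% / 4.9% |
| 20% vs 10% | 0.3 / 0.5 | -1.4 / -2.1 | 5.1% / 5.7% |
| 30% vs 10% | 0.3 / 0.5 | -2.4 / -4.1 | 6.2% / 8.6% |

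With ρ = 0 the difference is about zero at every rate.

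Closed-form check: excluding a fraction p shifts the mean of those who remain by -ρ × 27 × k(p), where k(p) = φ(z₁₋ₚ)/(1 - p). The values are k(0.1) = 0.195, k(0.2) = 0.350 and k(0.3) = 0.497.

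- 30% vs 10%, ρ = 0.5: -0.5 × 27 × (0.497 - 0.195) = -4.1.
- 20% vs 10%, ρ = 0.3: -0.3 × 27 × (0.350 - 0.195) = -1.3, against -1.4 simulated.

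Against the planned difference, 1.4/25 = 6% and 4.1/25 = 16%.

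The zero for equal rates also needs the same mechanism in both arms. If 10% are excluded in each arm but ρ is 0.5 in one and 0 in the other, the shift is 0.5 × 27 × 0.195 = 2.6 mg/dl.

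**The case against.** The best defence is that exclusion may mean no more than stopping capsules. The week-12 visit is scheduled and nowhere cancelled for excluded patients. The Safety section speaks only of stopping supplements. Overall adherence may be known only at the end, when week-12 data could already exist. Missing-data handling may be set out in a fuller document. This is a fair reason not to claim that every excluded patient certainly lacks an endpoint. It does not remove the conflict: the adherence rule says excluded from the study, and nothing says follow-up continues.

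Dissatisfaction is in substance voluntary withdrawal. The 10% dropout allowance may cover it, and rewording cannot guarantee those data. That stands.

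Four stronger readings are tempting but unsupported:

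- **The adherence rule applies to the active arm only.** The Exclusion criteria name only curcumin-piperine, but Randomization and interventions refers to the supplements for all participants. Blinding of investigators and participants also makes a one-arm rule unworkable. The fault is inconsistent wording.
- **The trial becomes underpowered.** On the plan's own difference and SD it does not, as shown above.
- **The bias has a known direction or a large size.** Removing exactly the worst 15% of placebo patients and nobody from the active arm would shift the mean by 0.274 × 27 = 7.4 mg/dl, but that is an extreme case. The treatments named as examples are for blood pressure and lipids, not glucose.
- **A safety conclusion is planned from a group made free of adverse events.** The Discussion sentence is conditional on benefit, and the protocol's safety argument rests on earlier studies. Nothing says that events go unrecorded.

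**Conclusion.** The contradiction is real and should be corrected. The protocol states post-randomisation exclusions that, followed as written, undermine its own ITT analysis. Because outcomes are measured only at baseline and week 12, patients removed early would generally contribute no observed endpoint.

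The consequence is possible bias, not certain bias. Its size and direction depend on unstated exclusion rates and on how exclusion relates to outcome. The illustrated range, from about zero to -4.1 mg/dl, rests wholly on the assumed rates and correlations and on the glucose SD. It says nothing quantitative about OCTA vessel density, which the protocol calls its most important finding and for which it gives no SD.

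On safety, the supported conclusion is limited: ending follow-up of patients who report adverse events weakens any safety statement drawn from this trial.

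**What to change.** Reconcile Exclusion criteria, Randomization and interventions, Safety and Statistical methods so that stopping capsules, leaving the study and leaving the PP set are three separate things:

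1. Take the four post-randomisation items out of the exclusion criteria.
2. Ask every randomised patient who has not withdrawn consent to attend the week-12 OCTA, blood and anthropometric assessments, whether or not capsules are still being taken.
3. Analyse all randomised patients in the assigned group, and name this ITT analysis as primary.
4. Use the 80% adherence rule, worded identically for both arms, and the treatment-change rule only to define the PP set.
5. Report adverse events by arm in all randomised patients, and limit any safety statement from this trial to those data.

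When capsules should be stopped is for the investigators to decide; the point here is only that the sections must agree.

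The cost is mainly wording, since the week-12 visits are already planned. The ITT estimate will include non-adherers and may be slightly smaller. Recruitment began in February 2022, so data from patients already excluded may not be recoverable; their number, arm and reason should be reported.
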